**2.1 Procedures**

***2.1.1 Study site selection***

The MoHS and the Ministry of Social Welfare, Gender and Children's Affairs (MSWGCA) identified four potential study sites in three high burden districts (Western Area, Bombali, and Port Loko). To enable recruitment of recent survivors from districts with ongoing transmission, Freetown is identified as a suitable recruitment area, and the possibility of a 2nd site is under investigation. Preliminary information suggests that survivors treated in Kenema during the early phase of the epidemic may also be residents of Port Loko, since no ETU was established there initially.

The pilot study has been conducted at M34 in Freetown. The main study will continue at M34 in Freetown.

In addition the possibility to start up a 2nd study site is being investigated. Guiding principles for selection of a 2nd site are feasibility in terms of construction and staffing and availability to invite more recent survivors, as well as tail-end long term male survivors. Lungi Government Hospital, as well as other options such as expansion within the MoD network of health posts, are currently explored.

The study sites will be the setting for all initial and follow-up visits of survivor participants and the location for interviews, specimen collection, and risk reduction counseling regarding test results. Study participants will be referred to HIV and survivor services within the hospitals where the study sites are located.

**Specimen storage, transport and testing**

• All specimens will be kept cold and transported to the field laboratory for RT-PCR testing within 48 hours.

• Transport will be organized three times a week from the M34 hospital during the pilot study, and then daily from the study sites to the field laboratory.

• Transport routines will follow guidelines on safe handling and transportation of hazardous bio-materials, which are further detailed in page 70+ and in: [Guidance on regulations for the Transport of Infectious Substances](http://www.who.int/ihr/publications/who_hse_ihr_2012.12/en/)

• At the field laboratory, specimens will be split into three aliquots: one for RT-PCR, and two for frozen storage.

• Aliquots of specimens testing positive by RT-PCR will be appropriately packaged, labelled as Category I biohazards, and shipped internationally under appropriate infection control precautions to CDC in Atlanta, GA, USA. The remaining specimen aliquot will remain in frozen storage in Sierra Leone.

• Virus isolation will be performed outside Sierra Leone, at a BSL-4 laboratory facility (US-CDC Atlanta).

• Blood for further analyses by immunofluorescence assays will be stored at room temperature and transported for analyses within 48 hours.

***2.1.2 Study participants***

***A. Participant recruitment***

Survivor associations in each of the districts will be involved with the study implementation. A small group of survivors will be formed to serve as key informants for sensitization of the community and recruitment for the study.

In collaboration with the survivors association and the MSWGCA, a list of established EVD survivors will be selected in accordance with sample size criteria. These groups of established survivors will be invited to a meeting in their district where they will be informed about the study process and benefits by MSWGCA staff and/or survivor key informants. The interested participants will be asked to provide contact information and an appointment will be scheduled for their first study visit. In addition print and radio advertisements may be used to recruit for the study.

In addition, people living with HIV (PLHIV) who also are Ebola survivors will be invited to participate in a sub-cohort. The “network of HIV positives in Sierra Leone” (NETHIPS) and local networks who work with PLHV will be used to identify and reach out to participants. HIV counsellors will also encourage their clients who are EVD survivors to participate in the study.

**Pilot**

The recruitment of survivors for the pilot will be done on a voluntary basis with the help of the association of survivors in Freetown and before the sample for the main study is selected. A collaboration with the national survivors’ association has already been started and the organisation has been part of the formative work. The association foresees no challenges in recruiting participants for the pilot study.

**Main study**

Recruitment from

the ETUs

All adult patients discharged from an ETU during the recruitment period will be asked to participate in the study

Recruitment from survivor registry

Survivors will be contacted according to their duration of convalescence and their place of residence.

Recruitment from other sources

If the number of patients is not enough, an open cohort process where participants will be recruited by using local ETU records, survivor networks and services; community outreach, including radio solicitations, may also be considered.

PLHIV networks PLHIV EVD survivors will be contacted by PLHIV support groups and networks in addition to HIV counselors who were closely with them

***B. Participant enrollment***

General inclusion criteria are adults (>18) who have survived EVD, with time lags since disease further specified below. Survivors with experiences of experimental treatment during their EVD as well as any pregnant women will be included in the study.

Eligible study participants must demonstrate an EVD discharge certificate and a national photo identification card in order to be recruited.

In order to ensure survivor status and eligibility for the study, we may cross-check laboratory information as available.

Participants will receive a study ID card that will be used for verification of identity at subsequent study visits.

Exclusion criteria are age < 18, no verified EVD discharge certificate, inability, for any reason, to follow study information and consent procedures.

**Pilot**

Adult male (18 years or above) survivors will be enrolled if eligible, with assistance of the survivors association in Freetown and the collaborating hospital and clinic.

**Main study**

All adult men or women (18 years or above), discharged from an ETU during relevant time periods (please see sample distribution), holding a certificate of recovery, are eligible.

***Sample size calculations***

**Pilot study sample size:**

A maximum of 100 men (not based on sample size calculations in relation to power, but on feasibility for assessing study process and generating enough knowledge for main study) will be included with a target of 40% between 2 and 3 months convalescence period and 60% with over 3 months convalescence period. These men will be followed until they have provided two consecutive negative semen specimens within a 2 – 4 week interval, and may be merged with the main study cohort as needed.

**Main study sample size:**

The following is the rationale for estimating the sample size needed for body fluids other than semen, when hypothetically the prevalence of persistence will be low and approaching zero, and when there is a wish to ‘rule out’ the possibility of viral persistence at a given time point by way of independent specimen provided by participants at baseline. The below sample size calculations for a zero prevalence estimate hence refer to estimating a population proportion at a certain point (or period) in time (i.e. at a specified time since EVD onset).

For the primary outcome of live virus isolated in tissue culture, even one positive (live EBOV virus) outcome is of interest; as such a finding would be expected to have important implications for guidance to future caregivers, patients, and their families. Similarly, we would not want to conclude that there is no probability of persistent live EBOV virus in the fluids we test if, in reality (within the larger population), there is. Therefore, the primary power calculation of interest is the degree of confidence we can have in a null (no positives) result from our tissue culture testing. In other words, we need to know the upper confidence limit for a calculated proportion of 0% in our study.

There are several ways to calculate an upper bound for a 95% confidence interval for a 0% finding. The rule of thumb for the upper bound is 3/N, where N is the number of specimens tested.6 This method is accurate when the sample is sufficiently large. Calculating the upper bound precisely requires use of the binomial distribution. The table below lists the upper bounds for a 1-sided 95% confidence interval estimated using Stata SE V12.1

Numerator 0 0 0 0

Denominator 50 100 200 300

Upper bound 7.1% 3.6% 1.8% 1.2%

Lower bound 0% 0% 0% 0%

In line with the above, based on the assumption of a 1st sample period prevalence (0-3 months) of viral persistence in body fluids other than semen, approaching zero we aim for a sample of 100 total participants (50 men and 50 women), adding an additional 20% of participants to account for potential drop-out. We would then arrive at a 95% confidence interval in gender specific sub-analysis of 0-7.1% and if all specimens are negative for both sexes a collapsed group analysis with a 95% CI of 0-3.6%.

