More recently a Scottish nurse experienced a severe complication with meningitis where Ebola virus detected in the cerebrospinal fluid and blood approximately 10 months after recovering from the initial infection. This raised questions on the frequency of this event among the population of survivors, and whether virus persisting in the body could be detected intemittently. These questions have to be better documented for the population of Ebola survivors in the three countries.

Many questions remain on how to manage pregnancy and delivery in Ebola survivors. Pregnant women who develop EVD have many complications, which include high mortality and stillbirths. In a few cases, a miscarriage occurred after a woman had resolved EVD infection in the blood, and the fetus and amniotic fluid was found to have virus. Little is known about whether virus can persist in women who have recovered from EVD and became pregnant after recovery.

*Ebola survivors in Sierra Leone*

The current situation for Ebola survivors in Sierra Leone involves several survivors’ support groups, actively working to provide risk reductioncounseling and support of various qualities to survivors.

In addition, survivors’ clinics are available, which provide medical care for post-Ebola sequelae, together with counseling, including around sexual transmission. The survivors are provided job opportunities in different organizations for community engagement to educate on stigma of sexual transmission; social mobilization and contact tracing. These activities are run in collaboration with UNICEF and the national survivors’ association.

The situation in the recent past has been that male survivors were being locked up, shunned and stigmatized by the community, and some chiefs also suggested that male survivors should be jailed in order to prevent sexual transmission of EVD. Upon actions from the National Ebola response committee, the attorney general wrote a letter officially condemning the persecution of male survivors. Nevertheless, male survivors are especially keen on the outcome of this study to know when it is safe to be intimate with their partners.

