**Main study**

Entry into the study will begin with informed consent (Appendix 1a). The first study visit will include a standardized interview and collection of specimens. All interviews will take place

in a private room of the study clinic. All self-administered, blood and other body-fluid sample collections will be done in private at the study clinic, and a strict protocol for handling of bio- hazardous material will be followed. If any study participant recruited for the main study is HIV positive, s/he will instead be included in the PLHIV sub-cohort, and will be replaced in the main study.

Specimens will be tested for EBOV RNA by RT-PCR in Sierra Leone at the field laboratory. For the majority of the pilot study this took place at US-CDC field laboratory in Bo. This lab closed on 15-Oct-2015 and Chinese-CDC laboratory in Jui has now taken over the testing for the pilot study. If the US-CDC field laboratory opens in Freetown, pilot testing will return to US-CDC. For the main study, Chinese-CDC lab in Jui will conducted all RT-PCR and antibody testing. Participants with a RT-PCR positive result in any of the initial specimens will be invited to provide prospective specimens (repeat specimen collection) of each RT-PCR positive body fluid. The participant will also receive a follow-up interview at every subsequent study visit (refer to Annex 1). Once a participant has had two negative test results in a row, collection of that body fluid will stop. RT-PCR test results are estimated to be available within two weeks of specimen collection and will be shared with the study participant. Once a participant has had two consecutive negative test results for all body fluid specimens collected in this study, there will be no further follow-up. (Pending on results from the pilot study and findings of intermittent semen shedding, this may be revised to comprise more tests accordingly).

Any specimen positive for EBOV by RT-PCR will be frozen and shipped for culture/viral isolation in a BSL-4 laboratory facility at US-CDC Atlanta. The confirmatory results of viral culture will be reported back to participants when they are available.

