***2.2.2 Criteria for discontinuation of a participant***

1. The prospective data collection from a participant including specimen collection in the Main study will be discontinued when specimens from all relevant body fluids are negative (two negative RT-PCR test results at consecutive study visits constitute a negative, or else amended as per preliminary results.)
2. If the specimens test negative at the 3 and 6 month follow-up visits, no further visits will occur.
3. If male participants are unable to provide a semen specimen at 2 consecutive visits, they will be referred to specialized urological care via a survivor clinic. Additional eligible survivors may be recruited to replace these participants.

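### The 0–7.1% and 0–3.6% limits bound how often a single baseline specimen tests positive; they bound persistence in survivors only if one specimen never misses it

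*Combined protocol and SAP*

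**What the plan says.** Section 2.1.2, under Main study sample size, deals with body fluids other than semen. The aim is to rule out viral persistence at a given time since onset "by way of independent specimen provided by participants at baseline". The target is described as a population proportion at a point or period in time, and N counts specimens tested. The primary outcome is live virus in culture. The authors say they do not want to conclude that live virus cannot persist when, in the wider population, it does. The calculation of interest is therefore "the degree of confidence we can have in a null (no positives) result from our tissue culture testing".

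The table is introduced by "The table below lists the upper bounds for a 1-sided 95% confidence interval estimated using Stata SE V12.1" and reads "Denominator 50 100 200 300" against "Upper bound 7.1% 3.6% 1.8% 1.2" (per cent). With 50 men and 50 women evaluable, the plan quotes 0–7.1% by sex and 0–3.6% pooled. Nothing is said about a specimen that misses virus.

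Elsewhere the plan does not treat one negative as conclusive:
- Section 2.2.2: "two negative RT-PCR test results at consecutive study visits constitute a negative".
- Main study structure chart: negative specimens are re-sampled at visit 2 to confirm negativity.
- Section 2.2.1: a first negative breast-milk result needs a confirmatory test.
- Sub-objectives and Section 7: results at 3 and 6 months are examined for re-detection after two negatives.

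On intermittent detection, Section 1.1 asks "whether virus persisting in the body could be detected intemittently". Section 2, Main study, makes the two-negative rule conditional on pilot results: "findings of intermittent semen shedding, this may be revised to comprise more tests accordingly".

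**The concern.** A zero-event limit based on one specimen per person bounds the probability that one specimen tests positive. To turn it into a bound on the share of survivors who carry virus in that fluid, the chance that one specimen detects a carrier must be known. Using the limit unchanged sets that chance to 1.

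The plan's wording moves from the first quantity to the second when it speaks of ruling out persistence. It also requires confirmation of every negative, which is hard to square with a detection probability of 1. Culture inherits the problem, because Section 2 sends only RT-PCR-positive specimens for isolation: a specimen missed by RT-PCR is never cultured.

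These are the only precision figures given for the main study, and Sections 10 and 14 say that the results will inform recommendations. If 0/50 is read as at most 7.1% of survivors, any error lies in the direction of too much reassurance.

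**Working it through.** **Inputs.** From Section 2.1.2: zero positives in 50, 100, 200 or 300; printed limits 7.1%, 3.6%, 1.8%, 1.2%; label one-sided 95%; one baseline specimen per person and fluid. Assumed, because the documents give no value: Se, the probability that one specimen from a person with persistent virus tests positive, taken as 0.9, 0.8, 0.7 and 0.5. False positives are ignored.

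**1. Reproduce the printed limits.** For zero events the exact limit is U = 1 − a^(1/n).
- a = 0.025: 7.11%, 3.62%, 1.83%, 1.22% for n = 50, 100, 200, 300. All four printed figures match.
- a = 0.05: 5.82%, 2.95%, 1.49%, 0.99%.

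The printed figures are therefore one-sided 97.5% limits (the upper end of a two-sided 95% interval), although labelled one-sided 95%.

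**2. Move from specimens to persons.** If a share p of survivors has persistent virus, one specimen is positive with probability p × Se, and the chance of 0/n is (1 − p × Se)^n. Setting this equal to a gives p = U/Se. For example, 7.11%/0.8 = 8.9%.

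**3. Confidence if 7.1% is kept as a bound on persistence.** This is 1 − (1 − Se × 0.071)^50. The 3.6% figure with n = 100 gives practically the same values.

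**4. Two specimens per person.** If the two are independent given persistence, Se is replaced by 1 − (1 − Se)²: 0.99, 0.96, 0.91 and 0.75.

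| Assumed Se | Limit, 0/50 | Limit, 0/100 | Confidence of 7.1% | Two specimens, 0/50 | Two specimens, 0/100 |
|---|---|---|---|---|---|
| 0.9 | 7.9% | 4.0% | 96.3% | 7.2% | 3.7% |
| 0.8 | 8.9% | 4.5% | 94.6% | 7.4% | 3.8% |
| 0.7 | 10.2% | 5.2% | 92.2% | 7.8% | 4.0% |
| 0.5 | 14.2% | 7.2% | 83.6% | 9.5% | 4.8% |

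Limits in the table are at the 97.5% level, as printed. At a true one-sided 95% level the single-specimen limits run from 6.5% (Se 0.9) to 11.6% (Se 0.5) for 0/50, and from 3.3% to 5.9% for 0/100.

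**5. Break-even against the label.** The printed figure keeps one-sided 95% confidence while U(0.05)/Se does not exceed it: Se ≥ 5.82/7.1 = 0.82 for n = 50, and 2.95/3.6 = 0.82 for n = 100.

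**6. Can Se be estimated from the study?** An obvious idea is to take the specimens collected before a participant's last positive and use the share of them that is positive. The two-negative stopping rule spoils this. Take a persister with true Se 0.5, independent specimens and at most three visits. The eight sequences are equally likely. The two that start with two negatives stop without a positive, and + − − has no specimen before its last positive. The other five (+++, ++−, +−+, −++, −+−) supply 2 + 1 + 2 + 2 + 1 = 8 specimens before the last positive, of which 2 + 1 + 1 + 1 + 0 = 5 are positive. The estimate is 5/8 = 0.63 instead of 0.5. With longer follow-up under the same rule it rises to about 0.69.

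**The case against.** **The target is defined, and the limits are valid for it.** Sections 1.2.4 and 7 name the period prevalence in first/baseline samples, and the sample-size text says that N counts specimens. This stands. The limits are not wrong as limits on baseline positivity; the gap opens only when they are used to rule out persistence.

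**Intermittent detection.** A reader might infer that the protocol expects it. It does not. Section 1.1 poses a question after one case involving cerebrospinal fluid and blood. The design text makes extra tests contingent on findings in semen, which this calculation excludes. The point rests instead on the confirmation rules, which cover every fluid. Those rules show that one negative is not accepted as absence, but they give no value for Se.

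**Size against the stated level.** A reader might infer that the stated confidence is simply too high, measured against a 2.5% error. The plan states no 2.5%; that level is only implied by the figures. Against the labelled 5%, the printed limits hold down to Se of about 0.82.

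**Enrolment.** The cohort table plans 120 men and 120 women, that is, 100 per sex and 200 pooled after the 20% allowance (100 × 1.2 = 120). The plan's own table then gives 3.6% and 1.8%; at Se 0.5 these become 7.2% and 3.7%, close to the figures quoted. This is a fair point about size, but it depends on a second site that Section 2.1.1 describes as still under investigation. It also leaves the meaning of the limit unchanged at any N.

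**Safeguards.** Re-sampling, the 3- and 6-month visits and the internal human control in Section 2.2.3 all help. The control detects an inadequate specimen, not a carrier whose specimen holds no detectable virus. The repeat specimens do not enter the calculated limit.

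**Culture.** A reader might infer that cold holding, freezing and shipping lower culture yield. The documents describe the handling but report no loss, so no figure here relies on it.

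**Conclusion.** The point holds in a limited form. The 7.1% and 3.6% limits are correct one-sided 97.5% limits on the proportion of single baseline specimens that test positive. As limits on the share of survivors with persistent virus they need an unstated Se of 1. For assumed Se from 0.9 to 0.5 they would be 7.9–14.2% and 4.0–7.2%. Whether confidence falls below the labelled one-sided 95% depends on whether Se is below about 0.82, which the documents do not settle.

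The results assume a common Se across persons and no false positives. The two-specimen figures also assume independent specimens and are optimistic if the same person tends to be missed repeatedly. The plan contains no decision rule declaring a fluid safe, so this concerns what a null result may be said to show, not a planned wrong decision. It is worth correcting because the correction is cheap.

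**What to change.** In Section 2.1.2 (Main study sample size) and Section 7:

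1. Label the zero-event limits as upper limits for virus detected in a single baseline specimen, and give their actual confidence level.
2. Base any statement that persistence is ruled out on limit/Se, tabulated by fluid over a stated assumed range such as 0.5–0.9.
3. Also report an RT-PCR limit using the protocol's own two-specimen definition of negative, with participants who gave both specimens as the denominator. The flow-chart text and the specimen projections (120 of each routinely sampled fluid per sex at visits 1, 2 and 3) already plan the repeats. The narrower wording in Section 2 (Main study) and the opening of Section 2.2.1, which invites back those with a positive result, must be reconciled with that.
4. Do not estimate Se from specimens taken before the last positive. The stopping rule biases that estimate upward, it has no data when there are no positives, and it cannot serve for culture because RT-PCR-negative specimens are not cultured.

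The cost is a few lines of text, one extra table and less favourable stated bounds. No extra participants or specimens are needed.
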